## Abstract

**Background:**

Postpartum depression (PPD) affects 30–50% of women with a history of previous depression or bipolar disorder and 8% of women with no history of depression. Negative cognitive biases in the perception of infant cues and difficulties with emotion regulation are replicated risk factors. Current interventions focus on detecting and *treating* rather than *preventing* PPD. The aim of this randomized controlled intervention trial is therefore to investigate the potential prophylactic effects of prenatal affective cognitive training for pregnant women at heightened risk of PPD.

**Methods:**

The study will enrol a total of 292 pregnant women: 146 at high risk and 146 at low risk of PPD. Participants undergo comprehensive assessments of affective cognitive processing, clinical depressive symptoms, and complete questionnaires at baseline. Based on the responses, pregnant women will be categorized as either at high or low risk of PPD. High-risk participants will be randomized to either prenatal affective cognitive training (PACT) or care as usual (CAU) immediately after the baseline testing. The PACT intervention is based on emerging evidence for efficacy of affective cognitive training approaches in depression, including cognitive bias modification, attention bias modification, mindfulness-inspired emotion regulation exercises, and working memory training. Participants randomised to PACT will complete five individual computerised and virtual reality-based training sessions over 5 weeks. The primary outcome is the difference between intervention arms in the incidence of PPD, assessed with an interview 6 months after birth. We will also assess the severity of depressive symptoms, rated weekly online during the first 6 weeks postpartum.

**Discussion:**

The results will have implications for future early prophylactic interventions for pregnant women at heightened risk of PPD. If the PACT intervention reduces the incidence of PPD, it can become a feasible, non-invasive prophylactic strategy during pregnancy, with positive mental health implications for these women and their children.

**Trial registration:**

ClinicalTrials.gov NCT06046456 registered 21-09-2023, updated 08-07-2024.

**Supplementary Information:**

The online version contains supplementary material available at 10.1186/s13063-024-08316-1.

## Background and aim

Postpartum depression (PPD) is a severe mental illness with a prevalence of around 8% for women with no history of depression [1, 2] and 30–50% for women with a history of previous depression or bipolar disorder (mania and depression) [3–7]. Multiple factors are associated with risk of PPD, including a history of depression, unwanted pregnancy, low emotional support, low socio-economic status [8] pregnancy complications [4, 9–11], weak attachment feelings to the unborn child [12, 13], and emotion regulation difficulties [14]. Emerging evidence indicates that negative cognitive bias in the perception of infant cues and reactivity to infant distress plays a key role for the risk of PPD. For example, we showed that more negative ratings of infant crying during pregnancy were associated with a substantially increased risk of PPD with an odds ratio of 3.75 [15]. This finding is in line with evidence that negative cognitive bias is a risk and maintaining factor for depressive episodes [16, 17]. Pregnant women at known risk of PPD are commonly offered prophylactic *pharmacologic* interventions, most commonly with selective serotonin reuptake inhibitors (SSRIs) [18]. However, many pregnant women are reluctant to accept pharmacological interventions due to their potentially harmful effects on the foetus [19–21]. Psychological interventions, including talk therapy, psychoeducation, and midwife consultations, have been found to reduce PPD symptoms [22–26]. However, these interventions generally focus on *detecting and treating* rather than *preventing* PPD [27]. *Psychological preventive* strategies in pregnant women *before* PPD onset are thus urgently needed.

Mothers with PPD display more negative and/or flat facial expressions and fewer expressions signalling comfort, excitement, and happiness during mother-infant interactions [28–30] and show difficulties with regulating their own and their infant's emotions [31]. Further, more depressive symptoms have been associated with greater self-focus and lower levels of caregiving warmth in mothers [32]. Moreover, PPD may disrupt normal, rewarding behavioural synchrony between mother and infant, as evidenced by low levels of mutual gaze and affective touch between mothers with PPD and their infants [33]. At a neural level, mothers with PPD show reduced activation in response to infant stimuli in brain areas associated with reward, empathy, and emotion regulation including the orbitofrontal cortex, insula, and dorsal anterior cingulate cortex [34]. We found that mothers with remitted recurrent depression displayed more negative facial expressions when listening to infant cries, preferential visual attention toward sad (versus happy) infant faces and attentional avoidance of intense infant emotions on computerised tasks compared to never-depressed mothers [35]. Importantly, these negative affective cognitive biases were associated with *less maternal sensitivity* in mothers’ real-life interactions with their infants as well as lower scores for the infants on cognitive, communicative and motor development [35]. Another study found that negative cognitive responses to computerized infant stimuli mediated the link between maternal depression symptoms in pregnancy and adverse maternal behaviours toward their own infant one year after birth. These behaviours include intrusiveness, flat affect, and both covert (e.g. sarcasm) and overt (e.g. yelling) forms of hostility [36]. Such behaviours likely increase infant stress levels and withdrawal behaviour and hamper infants’ experience of positive emotions and their acquisition of emotion regulation abilities [37–39]. Aberrant affective cognition therefore seems to be a key treatment target to improve both mothers’ and their infants’ mental health.

Preliminary evidence points to the potential of several effective cognitive training approaches to reduce the risk of PPD. In a pilot study, cognitive bias modification (CBM) reduced negatively biased perceptions of infant distress in mothers with PPD [40]. No study has been conducted of computerised attentional bias modification (ABM) in mothers with or at risk of PPD, however, two studies of patients with depression found that two–three sessions of ABM were able to reduce negatively biased processing of emotional faces [41, 42]. A study of mindfulness-inspired emotion regulation exercises for mothers with PPD, anxiety or stress showed improvement in these mothers’ ability to remain calm and display empathic, well-regulated, and sensitive behaviour towards themselves and their infants [43]. Further, mindfulness was found to enhance adaptive vs. ruminative self-focused attention [44] and to increase precuneus-subgenual anterior cingulate cortex functional connectivity and amygdala–temporal pole functional connectivity, when mothers listened to infant cries [45]. Finally, there is emerging evidence indicating that enhancing working memory abilities through cognitive training results in better emotion regulation abilities across psychiatric diagnoses [46]. Such working memory training may have beneficial effects on mothers’ interaction with their infants because of the association between better emotion regulation abilities and less harsh parenting [47, 48].

### Aims and hypotheses

The aim of this randomized controlled trial (RCT) is to investigate the potential prophylactic effects of a short-term (5 weeks) prenatal affective cognitive training (PACT) intervention that combines computer and virtual reality-assisted techniques compared with care as usual (CAU) for pregnant women at heightened risk of postpartum depression (PPD). Furthermore, pregnant women who do not meet the inclusion criteria for the high-risk group, are included in the study and assessed at baseline during pregnancy and follow-up after birth. This allows us to explore the risk factors that predict PPD among all pregnant women. We hypothesize that (i) PACT reduces the incidence of PPD during the first 6 months postpartum, and the severity of depressive symptoms during the first 6 weeks postpartum and (ii) the effect of PACT on PPD onset and depressive symptoms after birth is mediated by change in affective cognitive responses to infant stimuli.

## Methods

### Proof of concept pilot study findings

There was no formal patient and public involvement in the trial design. However, insights and participant feedback obtained in our smaller-scale non-randomized proof of concept study [49] informed the current investigation. We designed, programmed, and piloted a short-term multimodal prenatal affective cognitive training (PACT) for pregnant women at heightened risk of PPD, based on the different lines of emerging evidence for affective cognitive training approaches. Results from the pilot study of two weeks training (four sessions) in 16 high-risk pregnant women indicated that the intervention is feasible [49]; 12 of 16 participants completed all assessments, they generally gave positive feedback and reasons for dropout were pregnancy-related limitations of physical mobility. Despite the small sample size, the study revealed a statistically significant treatment-related reduction in prenatal negatively biased perception of infant stimuli and negative emotional reactivity toward infant cry, which correlated with lower symptoms of depression six months after birth [49]. The intervention further improved sensitivity to infant expressions of happiness, “infant-directedness” in women’s facial expressions and visual attention toward infants, which we hypothesise may have positive effects on the interaction with their infant after birth [49]. The current PACT RCT builds on these feasibility and proof-of-concept findings.

### Study setting

The PACT trial is conducted at the Neurocognition and Emotion in Affective Disorders (NEAD) Centre at the Psychiatric Centre Copenhagen, Frederiksberg, and at the Department of Psychology, University of Copenhagen, Denmark.

### Recruitment and enrolment

The trial will enrol a total of 292 pregnant women, including 146 women at a heightened risk of PPD and 146 women at a low risk of PPD. To identify eligible participants, we utilize the Danish Civil Registration (CPR) system to identify pregnant women (≥ 18 years of age) in their second or third trimester of pregnancy residing in the Capital Region of Denmark. The postdoctoral researcher on the study will invite potential participants via the online digital mailbox service used by 95% of the Danish population called “E-boks”. The invitation letter contains a link that interested participants can click to fill out their contact information and express their interest in an information meeting. For a visual representation of the recruitment process, please refer to Fig. 1.

**Fig. 1 Fig1:**
[figure not shown]
Recruiting sites, recruiting methods, and enrolment of participants. The purple lines refer to the enrolment of high-risk pregnant, and the green dotted lines refer to the enrolment of low-risk pregnant women

### In- and exclusion criteria

General inclusion criteria are second or third trimester pregnancy, age ≥ 18 years, and ability to speak and read Danish. Inclusion criteria for the high-risk pregnant group are either negative cognitive bias in emotional reactivity to infant distress (cut-off ≥ 96 on a scale from 0 to 100) *or* high-risk status according to the Antenatal Risk Questionnaire (ANRQ). The ANRQ assesses specific key psycho-social risk factors that increase the risk of developing PPD and considers pregnant women at high risk of PPD if they a) have a personal history of severe mental illness, b) have experienced childhood emotional, physical, or sexual abuse or c) if their total score on psycho-social risk factors is above the cut-off (> 23). Pregnant women diagnosed with a personality disorder will be excluded from randomization due to their higher treatment resistance [50]. However, they will still be included at baseline and follow-up after birth to explore the risk factors that predict PPD. Inclusion criteria for the low-risk pregnant group are the absence of a personal or family history of mental illness, the absence of negative bias and three or less of the additional risk factors mentioned above. General exclusion criteria are schizophrenia and current substance use disorder. Additionally, participants who have a score of 9 or more on the Hamilton Depression Rating Scale-6 items (HDRS-6), indicating moderate depression [51], will be postponed or excluded. This criterion is crucial for our prevention-focused approach, ensuring participants without active depression, allowing us to prioritize prevention over treatment.

### Statistical power calculation

In a previous study from our group on affective cognition in high-risk pregnant women, 50% went on to develop PPD [15]. On average, these women rated infant cries 0.47 standard deviations *more negatively* than high-risk women who remained healthy. Hence, 83% of high-risk women who went on to develop PPD, exhibited a negative bias in their responses to infant cries during pregnancy compared with 48% high-risk women who remained healthy. Therefore, targeting negative affective cognitive response to infant emotion may reduce the risk of PPD. Based on this PPD incidence of 50% [15], we aim to demonstrate a clinically significant reduction of the incidence of PPD from 50 to 25% (i.e. reducing the risk to half). To reach a statistical power of ≥ 80% for detecting this effect at a two-sided 0.05 alpha level, we need a sample of *n* = 58 pregnant high-risk women with complete data per intervention arm (https://clincalc.com/stats/samplesize.com). To accommodate for an expected dropout rate of up to 20% (as in our pilot study), we aim to include *n* = 73 women per treatment arm, i.e. *N* = 146 trial participants in total.

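### The 20% dropout allowance is attributed to a pilot that lost 25%; at the pilot's own rate, 146 women give about 78% power, not the stated 80% or more

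*Protocol article*

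**What the plan says.** The Statistical power calculation section plans for a "reduction of the incidence of PPD from 50 to 25% (i.e. reducing the risk to half") in the high-risk women. The target is given as "To reach a statistical power of ≥ 80"% "for detecting this effect at a two-sided 0.05 alpha level". This leads to 58 women per arm with complete data. The control rate is sourced: "In a previous study from our group on affective cognition in high-risk pregnant women, 50% went on to develop PPD".

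The step from 58 to 73 per arm, 146 in total, is justified by one clause: "To accommodate for an expected dropout rate of up to 20% (as in our pilot study"). No other basis for the 20% is given.

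The pilot is described under Proof of concept pilot study findings. It enrolled 16 high-risk women for four sessions over two weeks, and "12 of 16 participants completed all assessments". The same sentence goes on to explain the dropout by limited mobility in pregnancy, so the article itself treats the non-completers as dropouts.

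**The concern.** Twelve completers out of 16 is 75%, so the pilot's dropout was 25%. The article presents 20% as a ceiling and names the pilot as its source, yet the pilot lies above that ceiling. One input to the sample size therefore contradicts the only evidence cited for it.

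The stated power is at stake. The primary outcome is a single yes/no diagnosis, and this calculation is what a reader will use to judge a non-significant result. If the allowance for loss is smaller than the cited evidence supports, the claim of at least 80% power is not supported by the article's own pilot data.

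**Working it through.** **Inputs.** From the Statistical power calculation: control rate p1 = 0.50, PACT rate p2 = 0.25, two-sided alpha 0.05, power at least 80%, dropout 20%, 73 per arm. From the Study design section: 1:1 allocation. From the pilot section: 12 completers of 16.

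**Step 1: reproduce the plan.** Two proportions, pooled variance under the null, no continuity correction, with mean rate 0.375 and d = 0.25:

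n = [1.960 × √(2 × 0.375 × 0.625) + 0.842 × √(0.50 × 0.50 + 0.25 × 0.75)]² / d²

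= [1.960 × 0.6847 + 0.842 × 0.6614]² / 0.0625 = 57.7, so 58 per arm.

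Inflation: 58 / (1 − 0.20) = 72.5, so 73 per arm and 146 in total. All three figures agree with the article.

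**Step 2: power at 58 per arm.**

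Power = Φ[(0.25 × √n − 1.960 × 0.6847) / 0.6614]

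At n = 58 this is Φ(0.850) = 80.2%.

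**Step 3: the pilot's dropout.** (16 − 12) / 16 = 4/16 = 25%.

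**Step 4: put 25% into the plan.** 73 × 0.75 = 54.75 completers per arm. Power = Φ(0.768) = 77.9%. With whole numbers it is 77.3% at 54 and 78.1% at 55.

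**Step 5: what would keep 58 completers.** 58 / 0.75 = 77.3, so 78 per arm and 156 in total, which is 10 more women.

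**Step 6: the margin.** 80% power needs 57.67 completers per arm, and 57.67 / 73 = 0.79. Power is below 80% once dropout exceeds about 21%.

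**Check on the approximation.** Exact enumeration of the uncorrected chi-square test gives 79.9% at 58 per arm, 78.9% at 55 and 77.9% at 54. The conclusion does not depend on the normal approximation.

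**Sensitivity to the control rate (a remark, not an error).** Same formula, with the risk still halved:

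| Control vs PACT | Power, 58 per arm | Power, 55 per arm |
|---|---|---|
| 50% vs 25% | 80% | 78% |
| 45% vs 22.5% | 73% | 71% |
| 40% vs 20% | 66% | 63% |
| 35% vs 17.5% | 57% | 55% |
| 30% vs 15% | 49% | 47% |

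With a fixed difference of 25 points the direction reverses: 40% vs 15% gives 86% at 58 per arm.

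**The case against.** **The pilot cannot separate 20% from 25%.** This is true. The exact 95% interval for 4/16 runs from 7% to 52%, and if the true completion rate were 80%, 12 or fewer completers out of 16 would occur about 40% of the time. A planning value of 20% is therefore reasonable. But the article does not say that 20% is compatible with the pilot. It says that 20% is what the pilot showed, and as an upper limit. The imprecision is no support for a ceiling below the observed value.

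**Pilot non-completion is not the same as loss of the primary outcome.** This also has force. The pilot counted women who completed every assessment, and the losses were put down to mobility in pregnancy. The trial's primary outcome is one interview six months after birth, which may be done by telephone (Procedure section). Loss on it could well be lower. That would be a sound basis for 20%, but the article does not offer it. The pilot was also shorter than the trial, but nothing in the article shows which way this moves dropout.

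**Imputation is planned.** The Statistical analyses section does plan it. The 58 per arm is nevertheless defined as women with complete data, so the dropout allowance has to stand on its own.

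**A stronger reading: the control rate is wrong too.** A reader might infer that 50% conflicts with the article's own background figure, "30–50% for women with a history of previous depression or bipolar disorder", or that it is diluted because women can enter on "negative cognitive bias in emotional reactivity to infant distress" alone, given the 8% quoted for women with no history of depression. The documents do not support either inference. The 50% comes from the group's own high-risk cohort and lies within the 30–50% range, at its top. That range describes women with a psychiatric history, whereas entry to the trial is wider. The 8% is not a rate for women selected on bias, abuse history or psychosocial score, and the article does not say what share of the sample enters without a psychiatric history. The low powers in the table also depend on keeping the halving fixed.

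**Conclusion.** The concern holds for the dropout input. The article cites its pilot for dropout of up to 20%, and that pilot lost 4 of 16, or 25%. At 25%, 146 randomised women give about 78% power for 50% vs 25%, about two points below the stated minimum. This rests on the article's own rates and alpha, the pooled two-proportion formula, and the pilot's non-completion carried over to the primary outcome. The last of these is the article's own step, and it may be pessimistic.

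It would go too far to say that the sample size is miscalculated: 58, 73 and 146 all follow from the stated inputs. It would also go too far to say that 146 fails on the article's own figures because of the control rate. The control rate is a sourced assumption with no margin below it, and that calls for at most a sensitivity remark.

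**What to change.** Choose one of two corrections in the Statistical power calculation:

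- State the pilot's dropout as 4/16 (25%), and restate power for 146 randomised women as about 78% for 50% vs 25%.
- Keep 20%, remove the reference to the pilot, and give the actual basis, for example the expected loss on the six-month interview given that it can be done by telephone.

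Optionally, add a line or the short table above showing power for control rates from 30% to 50%, and say whether the relative or the absolute effect is held fixed.

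The cost is one or two sentences. The first option makes the stated power slightly less favourable. Neither changes the design, the conduct or the analysis, and no extra recruitment is needed.

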### Randomization

Pregnant PPD high-risk women are randomized to PACT or care as usual (CAU) using the REDCap randomization module. We stratify randomization with age (above/below 30 years) and parity (primiparous v. multiparous). A researcher outside the group generated the allocation sequence by creating an allocation table with allocation in blocks of varying size using Sealed Envelope Ltd [52]. This allocation table is used by REDCap’s randomization module. The postdoc on the project conducts the randomization. Allocation concealment will be ensured as REDCap will not release the randomization code until the patient has been recruited into the trial and the “randomize button” in REDcap has been selected.

### Study design

The trial is a parallel-group, outcome-assessor-blind, superiority randomized controlled study with a 1:1 allocation ratio. See Fig. 2 for a flow chart of the study design. To ensure the transparency and completeness of the study design and conduct, we followed the Standard Protocol Items: Recommendations for Interventional Trials (SPIRIT) 2013 statement and included a SPIRIT figure and checklist (see Fig. 3 and Additional file 1: Table S1).

**Fig. 2 Fig2:**
[figure not shown]
Flow-chart of the study design

**Fig. 3 Fig3:**
[figure not shown]
Schedule of enrollment, interventions, and assessments

### Procedure

At baseline (T0), all pregnant women undergo a comprehensive (2-h) assessment of affective cognitive processing of infant stimuli and non-emotional cognition, clinical rating of depressive symptoms, and completion of questionnaires regarding attachment to the unborn child, bonding to own parents, emotional relationship with their partner, demographics, clinical history, and state- and trait anxiety (details below). Further, a hair sample is collected from women to assess cortisol levels as a biological measure of stress. Based on the responses on questionnaires and affective cognitive processing, pregnant women are categorised as either at high or low risk of developing PPD (see the “In- and exclusion criteria” section above for specific inclusion criteria for high- and low-risk groups, respectively). High-risk participants are randomized to either PACT or CAU immediately after the baseline testing. Participants in the active intervention group complete a total of five individual training sessions over a period of approximately 5 weeks (for details on the study design, see Fig. 2). Around 5-6 weeks after the baseline assessment, all high-risk pregnant women (in the PACT or CAU arms) undergo their second assessment (T1) of affective cognition and self-ratings, including attachment feelings to the unborn child. For women receiving PACT, this assessment takes place within 1 week after the fifth training session. Lastly, if they have not given birth yet, women in the intervention group are offered a *booster* training session approximately 6-8 weeks after their baseline assessment. If participants face challenges attending in-person sessions, for example due to the late stage of their pregnancy, we will offer to conduct two sessions over the telephone or an online meeting. While computer training will not be feasible in this format, we will emphasize the key points from previous sessions and guide them on how to maintain their progress through home-based exercises like mindfulness techniques.

One week after their due dates, participants receive an e-mail with a link to 5-min online questionnaires regarding the birth, the infant’s health and well-being and mothers’ potential experience of depressive symptoms. On a weekly basis during the first 6 weeks after giving birth, mothers receive links to an online questionnaire to assess their depressive symptoms.

Six months after birth, we assess the presence or absence of PPD with a diagnostic interview conducted in person or over the telephone. Mothers also fill out questionnaires regarding their emotional reactions when their infants cry, postpartum bonding, parental reflective functioning, parental stress, and infant development. We assess if they have used any of the strategies learned during the PACT intervention in pregnancy. Around 8–13 months after birth, we will invite mothers and their children to visit the Department of Psychology for a functional near-infrared spectroscopy (fNIRS), where brain activity in both the child and mother is measured simultaneously during an interaction. From this, we assess interpersonal neural synchrony, which is the correlation of the mother’s and child’s brain activity over time during social contact [52]. We will make a short video recording of the mother-infant interaction, which will be coded by researchers blind to group status. Finally, at this visit, we assess child development. The researchers conducting follow-up assessments are blind to group status.

